### Variables

*Predictors:*

- Motor skills as described in the main application
- Physical activity as described in WP 4

*Outcomes:*

Psychological wellbeing will be measured using the Strengths and Difficulties Questionnaire (SDQ) [7- 9]. The SDQ is a brief questionnaire measuring child and adolescent psychological wellbeing. The SDQ includes 25 items, divided into 5 scales (5 items each): 1) emotional symptoms, 2) conduct problems,

3) hyperactivity/inattention, 4) peer relationship problems and 5) pro-social behavior. The SDQ further includes an impact supplement that asks if the registered behavior is considered a problem and if overall distress, social impairment, burden and chronicity are experienced. The SDQ is widely used to screen for mental health difficulties and as an outcome measure of psychological wellbeing both in clinical practice and in research. A total difficulties score is generated by adding scales 1-4 together and has been found to function as a dimensional measure of child mental health [10]. The questionnaire is available for parent and teacher reporting of children in four different age groups: toddlers (age 2 to 4 years), preschool children (age 5 to 6 years), school children (age 4 to 10 years) and adolescents (age 11 to 17 years). A self-report version is available for adolescents (age 11 to 17 years) [8]. All questionnaires are available in Danish and normative data from Denmark is available for children aged 5 to 12 years [11].

In the RCT, parental and staff reporting will be sampled. The use of multiple informants is commonly recommended to provide the most complete picture of the child’s psychological wellbeing and mental health, as parents and teachers observe children in different contexts, where different behaviors may be exhibited by the child [12]. For the cohort study, the self-report questionnaire is added when the children are aged 11 years or older. The SDQ will be administered electronically to parents and preschool staff twice yearly during preschool and to parents and teachers annually throughout the school years, with the addition of the self-report questionnaire when the child is 11 years of age and older.

The SDQ is expected to take around 10 minutes to complete.

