### Objectives to be explored in the RCT

1. To estimate the effect of a motor skills intervention on motor skills, physical activity, cognition, language development and wellbeing for a subgroup of children at early developmental risk.
2. To look at specific barriers to, and facilitators of, participation of children at early developmental risk in the motor skills program.

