### Variables

A subgroup of children will be included in the sub-group of children at early developmental risk based on the following information and measures:

- - Information on early medical and psychiatric diagnoses is collected from parents at baseline and at the last follow-up before starting school. Afterwards, this information is collected yearly during the school years.
  - Strengths and Difficulties Questionnaire (SDQ) is completed as described in WP 6. Computerized algorithms have been developed to estimate the likelihood of a child’s having a psychiatric diagnosis based on symptom and impact scores derived from the SDQs [9]. These algorithms are used to generate likelihood ratings (either: unlikely, possible or probable) for four broad categories of disorder: conduct disorders, emotional disorders, hyperactivity disorders and any psychiatric disorder. The algorithm has been found to correctly identify 81-91% of children who definitely had the indicated clinical diagnosis and is described as sufficiently accurate and robust

to be of practical value [9]. In this study, a probable rating of any of the four categories of disorders is seen as an indicator of a probable developmental disorder and henceforth as early developmental risk.

Further, information on the children’s early social-emotional development and the staff observations of the children’s wellbeing will be collected in the Municipality of Svendborg in the same period. Staff evaluations of child wellbeing are systematically collected twice yearly following written guidelines for the evaluation [10]. Part of this evaluation is the discussion of four domains of child wellbeing (psychological and emotional, cognitive, social and physical). Based on these discussions, a rating of thriving, cause for concern or strong concern is made for the overall wellbeing of each child. These registrations will be available for the study.

Thus, the child is perceived as being at early developmental risk if:

- - Parents report having received a formal child psychiatric diagnosis for the child prior to or during the project period.
  - Parents report having received a formal medical diagnosis for the child, during the project period. The focus is on pervasive diagnosis such as deafness, CP and DS which is known to influence development more pervasively.
  - The SDQ algorithm indicates the likelihood of a psychiatric disorder on the basis of either the completed parent or staff questionnaire.

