  - Staff rate high developmental concern in the RCT period.

The child is perceived as having developmental difficulties (as an outcome) if:

- Parents report having received a formal child psychiatric diagnosis for the child.
- Parents report having received a developmentally pervasive medical diagnosis for the child.
- The SDQ algorithm indicates the likelihood of a psychiatric disorder on the basis of the completed child, parent or teacher questionnaire at the last point of data collection.

This broad inclusion and practical demarcation of developmental difficulties is used in order to get a broader understanding of the developmental mechanisms related to children at developmental risk.

The following covariates will be accounted for when analyzing the results: sex, age, socioeconomic status as well as estimated general intelligence and executive functions as described in WP 7.

Barriers and facilitators:

Barriers to, and facilitators of, implementation in relation to children at early developmental risk are investigated using observations of participation from the perspective of the child [13]. Child participation will be observed in different preschools, both in activities defined as part of the motor skills intervention as well as in a number of other activities. Further, semi-structured qualitative interviews [14] with staff in the preschools will be included to strengthen the understanding of potential barriers and facilitators associated with children at early developmental risk.

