### Analyses

The analytic strategies described in the other WPs will be repeated on the subgroup of children who are identified as having early developmental difficulties.

For the cohort study, longitudinal latent class analysis and latent class growth analysis will be conducted to describe the patterns of developmental difficulties.

To describe barriers to, and facilitators of, implementation of the motor skills intervention for children at early developmental risk, observations and interviews are analyzed using a phenomenological analytic approach [14] to understand the participation of the child.

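### WP 8's RCT subgroup of children at early developmental risk can be filled after the intervention starts, so randomisation no longer guarantees comparable arms within it

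*Protocol*

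**What the plan says.** Protocol, WP 8, Objectives to be explored in the RCT: objective 1 is an intervention effect on motor skills, physical activity, cognition, "language development and wellbeing for a subgroup of children at early developmental risk". WP 8, Analyses, adds: "The analytic strategies described in the other WPs will be repeated on the subgroup of children who are identified as having early developmental difficulties". Those strategies include the between-arm comparisons of WP 1, WP 6 and WP 7.

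WP 8, Variables, lists four routes into the subgroup, any one of which appears to be enough:

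- Psychiatric diagnosis: "Parents report having received a formal child psychiatric diagnosis for the child prior to or during the project period".
- Medical diagnosis: "Parents report having received a formal medical diagnosis for the child, during the project period".
- SDQ: "The SDQ algorithm indicates the likelihood of a psychiatric disorder on the basis of either the completed parent or staff questionnaire". No wave is named.
- Staff rating: "Staff rate high developmental concern in the RCT period".

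The same section says that information on diagnoses "is collected from parents at baseline and at the last follow-up before starting school". WP 6, Variables, says: "The SDQ will be administered electronically to parents and preschool staff twice yearly during preschool". WP 6 also makes the parent SDQ total difficulties score its RCT primary outcome and the staff score a secondary one.

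The two other subgroup analyses in the document, those of children with poor motor ability in WP 1 and WP 6, fix membership at baseline.

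**The concern.** A subgroup comparison in a randomised trial keeps the protection of randomisation only if membership is settled by information that allocation cannot have changed. Here at least two routes can respond to allocation.

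The SDQ is the instrument on which WP 6 looks for an effect. The WP 6 background also says that the programme may change peer and staff-child interactions. The staff rating is made by preschool staff. WP 1, Perspectives, describes staff being educated for the programme and each preschool applying it, so it is reasonable to infer that raters in intervention preschools know their allocation, although the document does not say so.

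If the intervention lowers SDQ scores, fewer children are flagged in the intervention arm, and those flagged have a higher underlying level of difficulty. The comparison then runs against the intervention. If trained staff become readier to voice concern, the bias runs the other way. All the WP 8 RCT estimates for at-risk children share this membership rule, so all are exposed.

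**Working it through.** The plan gives no sample size, power or effect figure for this subgroup, so there is nothing of its own to reproduce. The check has two parts.

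**1. Timing of each route**

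| Route | Window stated | Can arise after the intervention starts? | Could allocation plausibly change it? |
|---|---|---|---|
| Psychiatric diagnosis | before or during the project | Yes | Possibly |
| Medical diagnosis | during the project | Yes | Implausible for deafness, CP or DS |
| SDQ flag, parent or staff | none; SDQ twice yearly | Yes, as written | Yes, it is a WP 6 RCT outcome |
| Staff concern | RCT period | Yes | Yes |

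WP 6 gives RCT follow-up of 6 to 30 months. With half-yearly SDQs that means 6/6 = 1 to 30/6 = 5 post-baseline waves per child.

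**2. Illustrative size (simulation, 2,000,000 children, equal arms, no clustering)**

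The inputs below are assumptions, not figures from the documents.

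- Each rating is a stable level U plus independent error, with total variance 1 and correlation 0.6 between any two ratings.
- A rating flags the child if it exceeds the 90th centile of the control distribution (10% per rating).
- Two informants rate at baseline and at each of k later waves. A child is a member if any rating flags.
- In the intervention arm every post-baseline rating is shifted by -0.30 SD, which is the true effect.
- Estimate: within the subgroup, last parent SDQ regressed on arm and baseline parent SDQ.
- Attenuation = 1 - |estimate|/0.30.

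| Membership | Flagged, intervention v control | Estimate | Attenuation |
|---|---|---|---|
| Baseline only | 16% v 16% | -0.30 | 0% |
| Baseline + 1 wave | 20% v 24% | -0.30 | 0% |
| Baseline + 2 waves | 23% v 29% | -0.26 | 1 - 0.262/0.30 = 13% |
| Baseline + 3 waves | 25% v 33% | -0.25 | 1 - 0.246/0.30 = 18% |
| Baseline + 5 waves | 29% v 38% | -0.23 | 1 - 0.225/0.30 = 25% |

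Variations with five waves:

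- Rating correlation 0.4 gives -0.23, and 0.8 gives -0.25.
- A shift of 0.10 SD gives -0.07 against a true -0.10. The proportion is similar, but the absolute loss is only about 0.03 SD.
- A shift of zero gives 38% v 38% flagged and an estimate of 0.00.

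For an outcome with no true effect that correlates -0.5 with U, the subgroup shows a spurious difference, adjusted for baseline SDQ, of about 0.02 SD with one wave and 0.04 SD with five (shift 0.30). Across shifts of 0.10 to 0.30 and correlations of 0.4 to 0.8 it is about 0.01 to 0.05 SD. Without the SDQ adjustment it reaches about 0.08 SD at a shift of 0.30. With baseline-only membership it is zero within simulation error.

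**The case against.** The strongest defence is that the harm is conditional. Post-baseline membership biases the comparison only if allocation moves the flags, and the simulation shows no bias when it does not. For conditions such as deafness, CP or DS such an effect is implausible. Five waves is the maximum follow-up, and the simulation applies the full shift from the first wave although WP 1 describes a six-month phase-in. The larger figures therefore sit near the upper end. The SDQ criterion is undated rather than expressly post-baseline, and a SAP or the main protocol, neither of which is at hand, could name the wave. All of this stands, and it limits the size and certainty of the point. It does not remove it, because the staff and diagnosis routes state post-baseline windows in the protocol itself.

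A reader might infer more than the document supports:

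- *That the medical criterion shuts out conditions known before entry.* The wording differs from the psychiatric criterion, but the time phrase may attach to when parents report, and early diagnoses are collected at baseline. The wording is ambiguous, not a demonstrated exclusion.
- *That unequal follow-up adds to the bias.* Children followed longer have more chances to be flagged, but nothing shows that follow-up differs between arms.
- *That the outcome in cohort objective 2 should count only new diagnoses.* That would drop lifelong conditions from an outcome that WP 8 deliberately keeps broad.

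**Conclusion.** The point holds in a limited form. As written, the WP 8 RCT subgroup can be determined partly by events after the intervention starts, and two of its routes (SDQ and staff rating) could respond to the intervention or to staff involvement in it. Randomisation then no longer guarantees comparable arms in the subgroup.

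It would go too far to conclude that the arms are certainly not comparable or that every WP 8 estimate is biased. That needs an effect on the flags, which the documents make plausible but do not establish. On the assumed inputs, with a shift of 0.30 SD, attenuation of the subgroup SDQ effect runs from about 0% (one post-baseline wave) to about 25% (five). The spurious effect on an unaffected correlated outcome is about 0.01 to 0.05 SD after SDQ adjustment. The direction depends on whether the intervention lowers or raises flagging.

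This should be fixed, but it is not critical to the trial. The WP 1 primary outcome and all full-sample analyses are untouched.

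**What to change.** For the RCT analyses in WP 8, define early developmental risk from baseline information only, in line with the subgroups of WP 1 and WP 6:

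- psychiatric and pervasive medical diagnoses known at baseline, with wording that expressly includes those made before entry;
- the baseline SDQ, parent or staff form;
- a staff concern rating only if one made before the intervention starts is available. WP 8 says only that the staff registrations are collected in the same period, so this must be checked; if none exists, drop the route for the RCT.

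Keep the wider definition for the cohort objectives, and say which definition applies to which objective.

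The cost is a change of wording. Baseline diagnoses are already scheduled, and the SDQ serves as a baseline covariate in the WP 6 model. The price is a smaller subgroup and wider intervals: in the illustration, 16% of children are flagged at baseline against 29% to 38% ever flagged over five later waves.

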### Length of follow-up

The duration of the follow-up period will be 12 years, which cover three years in preschool and nine years in school.

### Analyses

The analytic strategies described in the other WPs will be repeated on the subgroup of children who are identified as having early developmental difficulties.

For the cohort study, longitudinal latent class analysis and latent class growth analysis will be conducted to describe the patterns of developmental difficulties.

To describe barriers to, and facilitators of, implementation of the motor skills intervention for children at early developmental risk, observations and interviews are analyzed using a phenomenological analytic approach [14] to understand the participation of the child.

### Perspectives

The project will bring new insight into the relevance of motor skills and physical activity for children at developmental risk. Understanding how motor skills and physical activity are associated with trajectories of developmental difficulties and the extent to which early intervention might affect these trajectories is of great importance for developing efficient strategies for prevention or intervention associated with developmental difficulties.

